## Background

For children with refractory epilepsy, epilepsy surgery is a successful and widely accepted therapeutic option with postoperative seizure freedom rates ranging from 41 to 93 % [1, 2]. In patients who have been operated on and who have reached seizure freedom the ultimate goal is to discontinue antiepileptic drug (AED) use and to improve developmental capacities [3–5]. AEDs are known to have cognitive side-effects, particularly in children. Most affected cognitive functions are attention, vigilance and psychomotor speed [6–9]. AED reduction has been reported to improve cognitive processing under time pressure [8, 10], psychomotor speed and alertness [11–13], processing speed [14], verbal memory [15] and Intelligence Quotient (IQ) [9]. The growing body of evidence that cognitive functioning improves after AED withdrawal has increased awareness of the possible benefits of the earliest possible withdrawal of AEDs after epilepsy surgery. Two recently published studies [16, 17] showed that early withdrawal of drug treatment unmasks incomplete surgical success and AED dependency sooner, but not at the cost of worse long-term seizure outcome. Thus, early AED withdrawal would discern the few that require further AEDs from the many that can safely stop, without changing the chance of regaining seizure freedom. A pressing question is whether early AED withdrawal improves cognitive outcome measures, as compared to current care with usually later AED withdrawal. To answer that question we designed a pragmatic randomized clinical trial to investigate the benefits and safety of early AED withdrawal after epilepsy surgery in children. We hypothesize that 1) children who discontinue AED’s early have better cognitive scores, behavior and quality of life than those who discontinue late, particularly at 1 year after surgery (when 1 group is without AEDs and the other is still on AEDs), and maybe persisting from then on, and 2) early AED withdrawal is safe and does not cause more recurrences that are unresponsive to restart of medication, than late withdrawal.

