### Study objectives

The primary objective is to investigate whether early AED withdrawal improves cognitive function, in terms of attention and executive functions, compared to late AED reduction. The secondary objectives are to assess (improvement in) IQ, and safety, in terms of seizure recurrences, long-term seizure freedom and “seizure and AED freedom” of early versus late AED withdrawal. Seizure freedom will be defined as complete seizure freedom (including auras), expressed as Engel 1A or ILAE class 1 for at least 1 year [18, 19], and “seizure and AED freedom” as being seizure free without medication for at least 1 year. In addition, we will compare behavior, quality of life and other neuropsychological outcomes between the two AED withdrawal strategies.

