## Methods/Design

### Study design

The TimeToStop trial will be a European multicenter pragmatic randomized clinical trial. In the Netherlands the trial has been approved by the Medical Ethical Committee of the University Medical Center Utrecht, which is the leading ethical committee. Other participating centers are in the process of protocol submission and have not yet obtained definite approval. Only then, local patient recruitment will start. For every patient who will be included in the trial we will obtain informed consent. In the TimeToStop trial, index intervention is early withdrawal: AED withdrawal is started 4 months after surgery and completed within 8 months after start of withdrawal (thus, at latest 12 months postoperatively). Reference intervention is late AED withdrawal: tapering off medication starts at 12 months after surgery and completion should be within 20 months after surgery. For both treatment arms, the total tapering period is set at 8 months maximum and clinicians may decide which AED they want to taper first and at what speed they will reduce each individual drug. A tapering period of 8 months is considered reasonable, as from the retrospective TimeToStop (TTS) study [16] it could be calculated that patients who fulfill the inclusion criteria used on average 1.7 AEDs prior to surgery (range 0–3). The late (reference) starting point of AED tapering – i.e. 12 months – is based on current practice; the median interval between surgery and drug reduction in our retrospective European study was 12.5 months [16]. The 4 months’ time-point in the early withdrawal group is selected mainly because of logistical reasons. First, informing parents and recruiting patients needs time. Second, inclusion requires proof of early surgical success, which needs a certain time window to discriminate between acute postoperative (running-down) seizures and true seizure recurrence. Third, in some children clinicians may want to prove completeness of resection by performing a postoperative magnetic resonance imaging (MRI), for which a minimum follow-up time of a few months is required. For both intervention strategies, the treating physician is allowed to start tapering earlier if patients experience unacceptable side effects of prescribed AEDs. Rescue medication that is started preoperatively and withdrawn shortly after surgery, can be discontinued according to existing local routine practice, and will not be investigated in this study.

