#### Outcome parameters

Cognitive outcome: differences in EpiTrack scores, IQ scores and other continuous outcome measures of neuropsychological assessment will be analyzed using independent samples *t*-tests or other tests depending on distributions. EpiTrack and IQ differences will be assessed cross-sectionally to answer the primary research question. Additionally, longitudinal changes in EpiTrack measures and IQ compared to preoperatively will be assessed between both treatment arms using linear mixed models. We will calculate a number needed to treat, expressed as the number of patients required to taper drugs earlier to achieve one more patient with improvement in attention. Analyses will be considered statistically significant if 95 % confidence intervals for group differences do not include 0, compatible with a 2-sided *p* < 0.05. For chances of eventual seizure freedom and “seizure and AED freedom”; we will calculate a relative risk and a risk difference with 95 % confidence intervals. Chances of eventual seizure freedom and “seizure and AED freedom” will be compared between the groups at 24 months after surgery and at 20 months following start of AED withdrawal; for the early withdrawal arm this will be at 24 months and for the late withdrawal arm at 32 months.

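### Seizure and AED freedom needs a drug-free year, but it is compared at 24 months after surgery, when a late-arm child on schedule cannot yet have had one

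*Protocol article*

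**What the plan says.** All references are to the protocol article.

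- **Definition (Study objectives).** *Seizure and AED freedom* is defined "as being seizure free without medication for at least 1 year". It is a secondary outcome, and the Abstract lists it among those meant to confirm safety.
- **Early arm (Study design).** "AED withdrawal is started 4 months after surgery and completed within 8 months after start of withdrawal", so at the latest by month 12.
- **Late arm (Study design).** "tapering off medication starts at 12 months after surgery and completion should be within 20 months after surgery".
- **Taper length (Study design).** In both arms "the total tapering period is set at 8 months maximum".
- **Analysis (Outcome parameters).** For eventual seizure freedom and for *seizure and AED freedom*, "we will calculate a relative risk and a risk difference with 95 % confidence intervals". Both outcomes "will be compared between the groups at 24 months after surgery and at 20 months following start of AED withdrawal"; on the second time scale, "for the early withdrawal arm this will be at 24 months and for the late withdrawal arm at 32 months".
- **Rationale (Study design).** The 20-month look is meant to equalise AED-free time between the arms. The 24-month look is meant to show outcome two years after surgery whatever the AED-free time.

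**The concern.** An outcome that requires a year off drugs can be compared fairly only when both arms have had the chance to be off drugs for a year. At 24 months after surgery the schedule gives that chance to the early arm and withholds it from the late arm. The estimate then reflects the date of the visit and not any effect of the timing of withdrawal.

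The stated rationale for the 24-month look does not help here. Disregarding the length of AED freedom makes sense for plain seizure freedom. It cannot apply to an outcome that is itself defined by a length of AED freedom.

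The artefact favours early withdrawal, which is the trial's hypothesis, on an outcome presented as confirming safety. A reader who sees the relative risk and risk difference at 24 months could take a product of the schedule for a treatment effect.

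**Working it through.** **Inputs.** Start of taper: month 4 (early) and month 12 (late). Taper length *t*: above 0 and at most 8 months. Required drug-free time: at least 12 months. Looks: 24 months after surgery, and 20 months after start of withdrawal. All are from Study objectives, Study design and Outcome parameters.

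**The plan's own months.** 4 + 20 = 24 and 12 + 20 = 32. Both agree with the text.

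**Drug-free months at a look** = look month − (start month + *t*).

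| Taper *t* (months) | Early, month 24: 20 − *t* | Late, month 24: 12 − *t* | Late, month 32: 20 − *t* |
|---|---|---|---|
| 1 | 19 | 11 | 19 |
| 2 | 18 | 10 | 18 |
| 4 | 16 | 8 | 16 |
| 6 | 14 | 6 | 14 |
| 8 | 12 | 4 | 12 |

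At month 24 the late arm would reach 12 months only with *t* = 0, that is, with all drugs stopped on the first day of tapering. Late-arm success on schedule is therefore 0% by construction. At 20 months after start, both arms have 20 − *t* months, which is at least 12, so either arm can qualify.

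For the early arm the two looks are the same visit (month 24). The 24-month comparison thus differs from the 20-month one only in observing the late arm 8 months sooner (32 − 24 = 8), before it can qualify.

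**Size of the artefact.** Let *q* be the true success rate, equal in both arms, and *e* the share of late-arm children who come off drugs early enough to qualify by month 24. Both are assumptions. The expected risk difference is *q* − *qe* and the early:late relative risk is 1/*e*.

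- Full adherence, *e* = 0: the risk difference equals *q*, so 30, 50 or 70 points for *q* = 0.30, 0.50 or 0.70. The late arm has no successes, so the relative risk cannot be estimated. The value *q* = 0.70 corresponds to 30% recurrence; Safety monitoring expects less than 30%.
- *q* = 0.70 with *e* = 0.05, 0.10 or 0.20: risk difference 66.5, 63 or 56 points; relative risk 20, 10 or 5.
- If, in addition, a share *d* = 0.20 of otherwise successful early-arm children finish tapering after month 12, then with *e* = 0.20: 0.70 × 0.80 − 0.70 × 0.20 = 0.56 − 0.14 = 0.42, or 42 points.

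With 75 per arm (Sample size calculation), the chance of two-sided p < 0.05 without any true difference is above 99.9% for *q* = 0.30 and *e* = 0. It is still about 97.5% for *q* = 0.30 and *e* = 0.20, with the early arm on schedule.

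**The case against.** **The fair comparison is already planned.** The 20-month look is in the protocol, the article is open about what the 24-month look is for, and only one time point of one secondary outcome is affected. All of this stands, and it limits the consequences. It does not make the 24-month comparison of this outcome interpretable.

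**Real adherence will be imperfect.** Study design allows earlier tapering for unacceptable side effects and expects deviations, which are analysed as randomised. The Discussion foresees reluctance to accept the late arm. An early-arm child who uses the full 8 months has exactly 12 drug-free months and no slack. This stands too: 70 against 0 is an upper illustration, not a forecast.

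**The definition could be read more loosely**, as a year without seizures and merely off drugs at the visit. That would soften the point, but the wording attaches the year to being seizure free without medication.

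Three stronger inferences are tempting, and the document does not support them:

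- *That plain seizure freedom at 24 months is biased towards early withdrawal in the same way.* Both arms can meet it. A promptly controlled relapse at month 5 in the early arm counts as success and one at month 13 in the late arm as failure. But a relapse 13 months after taper start falls at month 17 in the early arm (failure) and at month 25 in the late arm (not yet seen). Time since taper start is 24 − 4 = 20 against 24 − 12 = 12 months, and the net direction is undetermined.
- *That the 20-month look is flawed because a relapse later than 8 months after taper start cannot be followed by a full seizure-free year.* That follows from the one-year definition and applies equally to both arms.
- *That the hypothesis that early withdrawal "does not cause more recurrences that are unresponsive to restart of medication" needs a new outcome.* Study objectives lists seizure recurrences separately. How response to restart is analysed may be left to the full protocol, and the article does not say whether it is recorded.

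**Conclusion.** The point holds for *seizure and AED freedom* at 24 months after surgery, and only there. As written, the definition, the late-arm schedule and the time of comparison cannot be reconciled: a late-arm child on schedule has 4 to under 12 drug-free months and cannot succeed, while an early-arm child on schedule can.

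With equal true success and full adherence, the spurious advantage for early withdrawal is about as large as the early-arm success rate, up to about 70 points under the assumed 30% recurrence in each arm. Early tapering for side effects or crossover in the late arm, and late completion in the early arm, would reduce it; the document gives no rates for these. The primary EpiTrack Junior analysis and its sample size are not affected, nor is the comparison of this outcome at 20 months after start.

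**What to change.** In Outcome parameters:

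1. State that *seizure and AED freedom* is compared inferentially only at 20 months after the scheduled start of withdrawal, that is, at month 24 in the early arm and month 32 in the late arm.
2. State that seizure status and drug status at 24 months after surgery are reported by arm descriptively, without a relative risk, risk difference or confidence interval for this outcome.
3. Keep plain seizure freedom at 24 months as planned, with a note that time since start of taper differs between the arms (20 against 12 months).

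If the looser reading of the definition was intended, Study objectives has to say so.

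The cost is a change of wording. The month-24 and month-32 assessments are already planned, so no visit is added. What is lost is one secondary comparison that would have looked favourable to early withdrawal.

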The trial’s primary outcome measure at 1 year after surgery is cognitive functioning, in terms of attention and executive functioning, which will be assessed using the EpiTrack Junior [20]. As secondary cognitive outcome measure, intelligence will be tested with the Wechsler Preschool and Primary Scales, the Wechsler Intelligence Scale for children, or the Wechsler Adult Intelligence scale, depending on the children’s age and capabilities; scores derived are Verbal (VIQ), Performal (PIQ) and Full-scale IQ, perceptual organization or reasoning and information processing speed index scores. We will measure baseline neuropsychological status maximum 3 months before surgery (t1), and thereafter at 12 months (±2 months) (t2) and 24 months (±2 months) (t3) postoperatively. Patients and/or parents will at all neuropsychological test points complete three types of questionnaires to assess the secondary outcome measures: the Child Behavior Checklist (CBCL) and the the Hague Side Effects Scale (HASES) [21] will be completed by the parents, and the Pediatric Quality of Life Inventory^TM^ (PedsQL™) will be completed by both parents and patients. This design will allow us to assess whether cognitive performance is better in the early AED-withdrawal group, with patients being AED-free at 1 year following surgery, compared to the group that is still on full medication at the first postoperative time point. It will also enable the study of differences at a later follow-up time point, when both groups have completely discontinued medication (t3) (Fig. 1). Seizure outcome will be assessed at the moment of randomization, as seizure freedom is an inclusion criterion, at 24 months after surgery, and at 20 months following start of AED withdrawal. This design allows us to assess differences in seizure outcome at equal AED-free intervals for both groups, and at 2 years after surgery irrespective of length of AED freedom.

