**Fig. 1 Fig1:**
[figure not shown]
Trial design. Flowchart of trial design; NPA, neuropsychological assessment

Patients will be allocated to treatment strategy by concealed blocked randomization and randomization will be stratified for preoperative IQ score and medical center. The primary goal of randomization is to achieve an AED treatment duration contrast. Therefore, physicians and patients allocated to an arm will be instructed to comply with that strategy. However, these intervention strategies will to a certain extent be in compliance with clinical practice, and allow “protocol violations” for the following instances: if patients have seizure recurrences in the period before scheduled AED withdrawal, they do not have to start AED withdrawal. The same applies to seizure recurrences that occur after start of tapering medication. Patients can restart medication and do not have to taper medication again, regardless of planned medication status. Notably, whatever “protocol deviations” will occur, patients will be analyzed as randomized (intention-to-treat principle).

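### Neither planned seizure comparison gives a fair as-randomized comparison of seizure-and-AED freedom; one early-arm contact at month 32 would supply the common horizon

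*Protocol article*

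**What the plan says.** The Study design section fixes the two schedules. In the early arm, "AED withdrawal is started 4 months after surgery and completed within 8 months after start of withdrawal"; in the late arm, "tapering off medication starts at 12 months after surgery and completion should be within 20 months after surgery". On duration: "For both treatment arms, the total tapering period is set at 8 months maximum".

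The Outcome parameters section says that both seizure endpoints "will be compared between the groups at 24 months after surgery and at 20 months following start of AED withdrawal", and spells out the second time point: "for the early withdrawal arm this will be at 24 months and for the late withdrawal arm at 32 months". The Study design section gives the purpose, which is to "assess differences in seizure outcome at equal AED-free intervals for both groups, and at 2 years after surgery irrespective of length of AED freedom".

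The Study objectives section defines both endpoints as a status held for at least one year: no seizures for seizure freedom, and neither seizures nor drugs for seizure-and-AED freedom. Analysis is by allocated arm whatever the later deviations. One permitted deviation matters here: "if patients have seizure recurrences in the period before scheduled AED withdrawal, they do not have to start AED withdrawal".

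**The concern.** Each time point equalizes one clock and leaves the other unequal. Month 24 equalizes time since surgery, and so time since randomization, but not time off drugs. The taper-aligned comparison equalizes time since the start of withdrawal, but reads the late arm 8 months later after surgery.

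For an endpoint that needs a drug-free year, this leaves no planned assessment at which both arms have the same horizon from randomization and both can reach the endpoint. Seizure-and-AED freedom is a named secondary safety outcome, and the authors expect no safety disadvantage from early withdrawal. A comparison that favours the early arm for reasons of timetable could be read as support for that expectation.

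**Working it through.** **Inputs.** Start of withdrawal at month 4 (early) and month 12 (late); maximum taper 8 months; assessments at month 24 and at start + 20 months (Study design, Outcome parameters). For illustration, 30% relapse over the 20 months after the start of withdrawal; the Safety monitoring section expects less than 30%. The documents give no relapse rate on drugs before tapering, so p, the proportion relapsing in the 8 on-drug months 4 to 12, is varied from 0 to 10% as an assumption.

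**1. The plan's own months.** 4 + 20 = 24 and 12 + 20 = 32. The stated figures reproduce.

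**2. Time on each clock, full 8-month taper.** Taper ends at 4 + 8 = 12 (early) and 12 + 8 = 20 (late).

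| Assessment (early / late) | Months from month 4 | Months since start of withdrawal | Months drug-free |
|---|---|---|---|
| Month 24 / 24 | 20 / 20 | 20 / 12 | 12 / 4 |
| Month 24 / 32 (planned) | 20 / 28 | 20 / 20 | 12 / 12 |
| Month 32 / 32 (not planned) | 28 / 28 | 28 / 20 | 20 / 12 |

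**3. Month 24, seizure-and-AED freedom.** A late-arm child who starts on schedule and tapers over d months is 24 − 12 − d = 12 − d months drug-free. That is below 12 for any d above 0, and is 4 for d = 8. Such a child cannot meet the definition, whatever the effect of timing. The early arm has 20 − d months, which is 12 even for d = 8. If every early-arm child without relapse qualified, the result under no true effect would be 70% against 0%. Only late-arm children who begin tapering ahead of schedule, as the article allows for unacceptable side effects, could qualify.

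**4. Month 24, recurrence.** Here the imbalance runs the other way. With a constant hazard after the start of withdrawal and no effect of timing, cumulative relapse is 30.0% in the early arm. In the late arm it is 1 − (1 − p) × 0.70^(12/20), which is 19.3% for p = 0 and 23.3% for p = 5%.

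**5. Taper-aligned comparison, seizure-and-AED freedom.** Suppose that children who relapse before tapering never start it, and that the others keep the full 30% risk afterwards. The late arm then succeeds in (1 − p) × 0.70 against 0.70 in the early arm, so the deficit is 0.70p: 0.7 points for p = 1%, 1.4 for 2%, 3.5 for 5% and 7.0 for 10%. If the children who relapse on drugs are the same ones who would have relapsed on tapering, the later risk falls to match and the deficit is zero.

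**6. Taper-aligned comparison, 1-year seizure freedom.** The look-back year is months 12 to 24 (early) and 20 to 32 (late), which is months 8 to 20 after the start of withdrawal in both arms. Let r be the share of earlier relapsers who have regained control before that year. Early: 0.70 + r(1 − 0.70^(8/20)). Late: (1 − p) × 0.70 + r(1 − (1 − p) × 0.70^(8/20)). For p = 10%, late minus early is −2.7 points at r = 50%, −0.9 at r = 70% and +1.7 at r = 100%. The sign is not fixed.

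**7. The proposed month 32, tested the same way.** Both arms can reach the drug-free year (20 and 12 months). The early arm has 8 more months since the start of withdrawal. Under the constant hazard of step 4, its cumulative relapse would be 1 − 0.70^(28/20) = 39.3%, against 1 − (1 − p) × 0.70 in the late arm: 30.0% for p = 0 and 33.5% for p = 5%. If relapse after tapering is largely over by 20 months, this gap closes.

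**The case against.** The offset is deliberate and explained. The article expects relapse mainly once withdrawal begins and argues under Safety monitoring that comparing arms at unequal withdrawal exposure is unfair. Two views with opposite limitations are both planned, and the on-drug months before the late taper are part of the late strategy. The look-back years are equally long. Month 32 in both arms brings back unequal time off drugs (step 7). All of this stands. It is a reason to keep the taper-aligned comparison, not a reason to do without a common horizon at which both arms can qualify.

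A reader might infer more: that reading the late arm 8 months later makes early withdrawal look safer by a definite number of points. The documents do not support that. Such a figure needs cumulative recurrence since randomization, whereas the Outcome parameters section compares 1-year status. It needs an on-drug relapse rate, and none is given. It also needs the late arm to carry an undiminished risk into tapering, although the Background says that early withdrawal reveals incomplete surgical success sooner, which suggests that some of the same children would relapse either way.

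It can also be said that follow-up of the early arm need not end at month 24, since the monitoring board counts recurrences every 3 months. But the article lists no outcome assessment for that arm beyond month 24, and a recurrence count does not establish drug status.

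**Conclusion.** The point holds for seizure-and-AED freedom. At month 24 it follows from the schedule and the definition alone: a late arm that keeps to its schedule scores zero, so the difference is as large as the early arm's whole success proportion (70 points under the 30% illustration). It assumes that the definition means a full year off drugs, as it reads.

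In the taper-aligned comparison, the extra on-drug months can lower the late arm's result, but by an unknown amount: 0 to 7.0 points over the assumed range, and near zero if the same children would have relapsed on tapering. For scale, with 75 per arm and 30% in each, the 95% interval for a risk difference is ±1.96 × √(2 × 0.3 × 0.7 / 75) = ±14.7 points. For 1-year seizure freedom the direction is uncertain. The primary EpiTrack comparison is not affected.

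**What to change.** Add one seizure and AED status contact for the early arm at 32 months after surgery. Compare both arms as randomized at month 32 for recurrence, seizure freedom and seizure-and-AED freedom. Keep the taper-aligned comparison (month 24 against month 32) beside it, with relapses before the start of withdrawal shown separately by arm. State that 1-year seizure-and-AED freedom at month 24 will not be interpreted as a between-arm comparison.

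Cost: 8 more months of light follow-up for 75 to 90 early-arm children (half of 150 to 180), with one telephone or routine-clinic contact each and no new test. The end of the trial need not move, because the late arm is already assessed at month 32, and the Trial status section reports that no patients had been included. The drawback is that at month 32 the early arm has had more time off drugs, so neither comparison should be reported without the other.
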